## Standard care

In the TC, there is a supervised and structured daily schedule in an environment free of substances. The standard care in the TC includes daily individual and group therapy sessions led by social workers and counselors. In addition, individuals have leisure and enrichment activities, etc.

### Procedure

Individuals with SUD consecutively admitted to the TC will be approached and invited to participate in the study. All assessments, will be administered by assessors blind to group allocation to minimize bias. Assessments will be performed in two sessions within one week and administration sequence will be counter balanced in two different orders to eliminate fatigue and attention span bias.

## Randomization

Following the T1 assessment participants will be stratified according to yes/no Attention deficit hyperactivity disorder (ADHD) based on The Adult ADHD Self-Report Scale-Version 1.1 (ASRS-V1.1)[73], a valid and reliable [74, 75] screening tool for ADHD. ADHD is prevalent in SUD population [76] and might affect intervention compliance and therefore will be controlled. Thereafter participants will be randomly allocated (using a simple block random allocation software) into the two arms. Allocation (1:1 ratio) will be concealed. Participants will be informed regarding their allocation by the research assistant who will not take part in the assessments or intervention.

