### Sample size

The sample size was calculated to (i) detect a minimally clinically important difference of the primary outcome measure of everyday (occupational) performance (COPM; see below) with 80% power and a significance level of 0.05, and (ii) to account for a 40% dropout. Thus 24 participants per group will be recruited providing a total of 48 participants for the study**.**

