## Data analysis

Descriptive statistics will be used to describe the participants in each group, in terms of their, demographic information and SUD parameters, primary and secondary outcome measures. Pre-intervention differences between the two groups will be analyzed using t-Test for independent samples (continuous measures) or Chi square (dichotomous measures). A repeated measures ((2)X4) analysis of variance ANOVA will be used to compare within- and between- group scores, for time (T1, T2, T3, T4) comparing the F-CaST to standard care and for interaction time*group effect.

To assess the clinical meaningfulness of the outcomes, the Partial Eta squared in ANOVA effect size will be calculated. Partial Eta squared is interpreted as the proportion of the total variability in the dependent variable that is accounted for by variation in the independent variable. ANOVA Partial Eta squared of 0.01, 0.06 and 0.14 are considered small, medium and large effect sizes (respectively).

Statistical significance will be set at p < 0.05, and all analyses will be conducted using SPSS for Windows version 27.0 (SPSS Inc, Chicago, IL). The transcripts of each of the four in-depth interviews will be analyzed using content analysis (an initial review, the development of mapping categories, and the building of a mapping categories tree) [77].

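### Randomisation is stratified by ADHD status, but the stated ANOVA omits the stratum and treats the pre-randomisation score as an outcome: valid, but generally less powerful than it could be

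*Protocol article*

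**What the plan says.** In the Randomization section, participants are classed by ADHD screening status after the T1 assessment and then allocated in blocks to the two arms. The reason given is that ADHD is common in this population and "might affect intervention compliance and therefore will be controlled".

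The Data analysis section names one inferential model for the scores: a repeated measures ANOVA with two groups and four visits (T1 to T4), "comparing the F-CaST to standard care and for interaction time*group effect". No ADHD term and no covariate is named. T1 is a level of the time factor. On baseline comparability it says: "Pre-intervention differences between the two groups will be analyzed using t-Test for independent samples (continuous measures", with chi-square tests for dichotomous measures.

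The Sample size section aims to "detect a minimally clinically important difference of the primary outcome measure of everyday (occupational) performance" "with 80% power and a significance level of 0.05", and "to account for a 40% dropout". It concludes: "Thus 24 participants per group will be recruited providing a total of 48 participants for the study".

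**The concern.** Stratified allocation balances ADHD between arms and so removes its contribution to the true variability of the group difference. A model without the stratum leaves that contribution in the error term, so the estimated standard error is larger than the design warrants.

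T1 precedes allocation, so no treatment effect is possible there. Counting it as an outcome visit pulls the group main effect towards zero and makes the interaction an omnibus test over three contrasts. It also gives up the precision that T1 offers as a covariate. Significance tests of baseline differences neither correct chance imbalance nor recover that precision.

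At stake is power in a small trial that expects to lose 40% of its participants. The article also does not say whether the main effect or the interaction decides efficacy.

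**Working it through.** **1. Completers and the plan's own figure.** 24 × (1 − 0.40) = 14.4, so about 14 per arm. The 24 cannot be reproduced, because neither the COPM difference nor its SD is given. Working back, 14 / 0.6 = 23.3, rounded up to 24. Fourteen per arm with 80% power at two-sided 5% implies d = (1.96 + 0.84) × √(2/14) ≈ 1.06 SD. The simulations use 1.10 SD, which allows for the t distribution.

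**Assumptions not in the documents:** equal correlation ρ between visits of 0.3, 0.5 or 0.7; half the men with ADHD, balanced across arms; an ADHD effect b of 0.8 SD where one is present. Results are listed in the order ρ = 0.3 / 0.5 / 0.7. Repeat simulations differ by a point or two.

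**2. Omitted stratum, group main effect.** A balanced binary factor adds b²/4 = 0.16 to the estimated variance but nothing to the true variance of the group difference. The variance of a man's four-visit mean is (1 + 3ρ)/4 = 0.475 / 0.625 / 0.775.
- Ratio of estimated to true SE: √(0.635/0.475) = 1.16; √(0.785/0.625) = 1.12; √(0.935/0.775) = 1.10.
- The nominal 1.96 cut-off acts as 2.27 / 2.20 / 2.15, so true type I error is about 2.3 / 2.8 / 3.1%. Simulation gives 2.2 / 2.8 / 3.1%.

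**3. Omitted stratum, time-by-group test.** An ADHD effect that is constant over all four visits cancels from within-person contrasts. Simulated type I error is then 4.5–5.6%, or about 4–4.5% with the Greenhouse-Geisser correction. If the effect appears only after T1, as one acting through compliance would, it is 3.0 / 3.2 / 2.5%. ANCOVA with T1 and ADHD gives 4.7–5.0%.

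**4. T1 as an outcome visit.** With no ADHD effect the interaction's type I error is 4.5–5.2%, so the test is valid. The cost is precision. At one follow-up visit, change from T1 has variance 2(1 − ρ) and ANCOVA has 1 − ρ². The ratio is (1 + ρ)/2 = 0.65 / 0.75 / 0.85. At 14 per arm and d = 1.06, power rises from 66% to 84%, 80% to 90%, and 95% to 97.5%.

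A sustained effect δ enters the group main effect as (0 + δ + δ + δ)/4 = 0.75δ. Simulated power for 1.10 SD at T2, T3 and T4:

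| Test | ρ = 0.3 | 0.5 | 0.7 |
|---|---|---|---|
| Time-by-group, 3 df | 67% | 83% | 97% |
| Group main effect | 86% | 76% | 68% |
| T2 adjusted for T1 | 82% | 88% | 96% |
| Mean of T2–T4 adjusted for T1 | ≥98% | ≥98% | ≥98% |

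**5. Adding ADHD to the adjusted model.** If ADHD acts only after T1, power for T2 adjusted for T1 rises from 76 / 84 / 95% to 82 / 89 / 98%. If its effect is constant, T1 already carries most of it. With ρ = 0.5 and a 0.8 SD treatment effect, power for the T2–T4 mean goes from 85% to 86%.

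**6. Other shapes of effect.** The T1-adjusted mean of T2–T4 has residual variance (1 + 2ρ)/3 − ρ² = 0.443 / 0.417 / 0.310, so its SE is √(2 × variance/14) = 0.252 / 0.244 / 0.210. The normal formula, a few points optimistic at this size, gives the power of that contrast below.
- Fading, 1.1 / 0.55 / 0 SD at T2 / T3 / T4 (mean 0.55): about 59 / 62 / 74%. The interaction has about 62 / 79 / 96% and the group main effect 23–34%.
- Building, 0.3 / 0.8 / 1.1 SD (mean 0.73): about 83 / 85 / 94%. The interaction has 57–93% and T2 adjusted for T1 only 12–17%.

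**The case against.** **A contradiction between sections.** A reader might infer that the article promises to control ADHD and then breaks the promise. The sentence stands in the Randomization section and can mean control by stratification alone, which the design delivers. The point is an analysis that does not match its design.

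**A condensed article.** A full analysis plan may list covariates, and the article does not exclude them. That carries some weight for the ADHD term. It carries less for T1, because the four-level time factor already fixes T1 as an outcome, and a plan using it as a covariate would have to replace the stated model.

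**Wrong error bars in general.** A reader might infer that both features invalidate the standard errors or risk false positives. Neither follows. Only the stratum omission affects standard errors, and it makes them too wide. Random dropout weakens even this, because completers need not stay balanced on ADHD. With 10 of 24 men lost at random per arm, simulated type I error is about 4.4% and 3.7% if ADHD explains 10% and 20% of the variance, against 3.8% and 2.8% with perfect balance.

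**T2 as the obvious primary contrast.** It ties with the interaction at ρ = 0.7, loses to the main effect at ρ = 0.3 for a sustained effect, and does badly if benefit builds. The article wants to verify stability and expects benefit at every assessment, so T2 is not the only defensible choice.

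**Baseline tests.** The article never says that they correct imbalance or select covariates. Replacing them is good practice and does not repair a stated error.

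**Conclusion.** The concern holds as a matter of efficiency and of matching the analysis to the design. Omitting the stratum makes the group main effect conservative if ADHD affects the outcome (true level about 2–3% for a constant 0.8 SD effect), and the interaction conservative (about 3%) only if that effect arises after T1. Treating T1 as an outcome leaves type I error intact but generally costs power. For a sustained 1.1 SD effect, the adjusted T2–T4 average gains between 1 and 31 points over the interaction (98 − 97 and 98 − 67) and at least 12 over the main effect (98 − 86). Part of the gain over the interaction comes from using one degree of freedom instead of three.

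The gain is not universal: if the effect fades, the interaction does better than the T2–T4 average. All sizes rest on an assumed visit correlation, ADHD effect, ADHD prevalence and effect shape, none of which the document gives. The T1 point does not apply to length of stay, which has no T1 value.

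**What to change.** - For COPM and other outcomes measured at T1, model T2–T4 by ANCOVA or a mixed model for repeated measures, with T1 score and ADHD stratum as covariates.
- For length of stay, adjust for ADHD stratum only.
- Name in advance the group contrast that decides efficacy, for example the T2–T4 average or a single visit. This is the sponsor's choice and should follow the expected course of benefit, since no contrast is best for every shape.
- Present baseline data by arm descriptively, without t-tests or chi-square tests.

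The cost is analysis wording and up to two degrees of freedom. Both covariates are already collected before allocation, so no new data or participants are needed. Choosing a deciding contrast is a substantive decision, because it settles which question the trial answers.

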## Data analysis

Descriptive statistics will be used to describe the participants in each group, in terms of their, demographic information and SUD parameters, primary and secondary outcome measures. Pre-intervention differences between the two groups will be analyzed using t-Test for independent samples (continuous measures) or Chi square (dichotomous measures). A repeated measures ((2)X4) analysis of variance ANOVA will be used to compare within- and between- group scores, for time (T1, T2, T3, T4) comparing the F-CaST to standard care and for interaction time*group effect.

To assess the clinical meaningfulness of the outcomes, the Partial Eta squared in ANOVA effect size will be calculated. Partial Eta squared is interpreted as the proportion of the total variability in the dependent variable that is accounted for by variation in the independent variable. ANOVA Partial Eta squared of 0.01, 0.06 and 0.14 are considered small, medium and large effect sizes (respectively).

Statistical significance will be set at p < 0.05, and all analyses will be conducted using SPSS for Windows version 27.0 (SPSS Inc, Chicago, IL). The transcripts of each of the four in-depth interviews will be analyzed using content analysis (an initial review, the development of mapping categories, and the building of a mapping categories tree) [77].

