EF have been recognized as a key predictor for effective goal achievement and high self-efficacy, and therefore intact EF are crucial for treatment compliance and rehabilitation success [7, 16, 17]. Evidence clearly demonstrates that deficits in EF reduce successful SUD rehabilitation, specifically of cognitive behavioral therapies commonly provided in SUD rehabilitation programs [6, 13]. Indeed, dropouts, especially from long-term treatment frameworks, were recognized as a serious challenge in the treatment of SUD [13, 18]. Specifically, the estimated therapeutic community (TC) dropout rates stands up to 71% [18, 19], emphasizing that EF should be an important neurocognitive target in SUD interventions. Importantly, a recent systematic review concluded that cognitive remediation has the potential to pave the avenue for improving cognition and treatment outcomes in SUD [6].

Information processing that underlies EF is directly related to sensory perception. EF, specifically inhibitory control, plays an important role in the way sensory input from the environment is processed [20, 21]. Although deficits in EF have been found to be associated with difficulties in sensory processing within various populations across the life span (e.g., children with Autism Spectrum Disorders [21]; attention deficit hyperactivity disorder (ADHD); adults with specific learning disabilities [24] and older adults [25], there is limited research regarding populations with SUD. We have recently reported Sensory modulation dysfunction (SMD) in 54% of individuals with SUD (*vs.* 11.7% in a healthy comparison group) and revealed that sensory over-responsivity is a major contributing factor in SUD phenomenon [25].

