### Behavior and length of stay in TC

Information regarding participant behavior (discipline, number of times being late for scheduled activities) will be collected from the TC counselors. Length of stay (days) residing in TC. The Longer time spent in the TC, the better**.**

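### The planned 2x4 repeated-measures ANOVA uses only men with all four assessments, so at the expected 40% dropout it discards data from about 19 of 48 randomised men and may compare selected completers

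*Protocol article*

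**What the plan says.** Apart from baseline t-tests and chi-square tests, the Data analysis section of the protocol article gives a single group comparison: "A repeated measures ((2)X4) analysis of variance ANOVA will be used to compare within- and between- group scores". It is specified "for time (T1, T2, T3, T4) comparing the F-CaST to standard care and for interaction time*group effect", with partial eta squared as the effect size, and "all analyses will be conducted using SPSS for Windows version 27.0". The article names no mixed model and no imputation.

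The Sample size section sets the number recruited "to account for a 40% dropout" and concludes: "Thus 24 participants per group will be recruited providing a total of 48 participants for the study". The Methods section, in the paragraph on the four assessments, gives high reported dropout as a reason why repeated follow-up matters.

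Length of stay is listed among the primary outcomes and defined as "Length of stay (days) residing in TC". The abstract and the Discussion both expect F-CaST to lengthen it. Under Randomization, allocation follows the T1 assessment, so every randomised man should have T1 scores.

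**The concern.** Classical repeated-measures ANOVA (GLM Repeated Measures in SPSS) needs a complete set of T1 to T4 scores and drops any man with a gap. A man seen at T1, T2 and T3 but not at T4 contributes nothing. The follow-up visits were added partly because dropout is high, yet this method cannot use them for the men who drop out.

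The second issue is comparability. Leaving the TC is a plausible main reason for missing a visit, and staying is an outcome that F-CaST is meant to improve. If so, the men analysed are selected after randomisation by something the treatment may change, and the two sets of completers need no longer be comparable. Enlarging the sample for dropout protects power; it does not remove selection.

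**Working it through.** **1. The plan's own figure.** Inputs from the Sample size section: 24 per group, 40% dropout, "with 80% power and a significance level of 0.05" (two-sided assumed). The article does not print the COPM difference or its SD, so 24 can only be solved backwards.
- Completers per arm: 24 x 0.6 = 14.4.
- Standardised difference detectable with 14 per arm: d = (1.96 + 0.84) x sqrt(2/14) = 1.06 (1.10 with the exact t distribution).
- Forward check: n = 2 x (1.96 + 0.84)^2 / 1.06^2, which rounds to 14; 14 / 0.6 = 23.3, rounded up to 24.

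The stated number is therefore consistent with a design that expects about 14 completers per arm.

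**2. Men kept and lost by the ANOVA.** This assumes that the 40% are the men who miss at least one assessment.
- Kept: 48 x 0.6 = 28.8, about 29.
- Lost: 48 x 0.4 = 19.2, about 19. Their T1 scores, and any T2 or T3 scores, go unused.

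**3. Precision.** Illustrative simulation, all inputs assumed: 24 per arm, COPM SD 1.8, correlation between visits 0.5, true effect 2 points, dropout depending on the last observed COPM score, retention about 49% to 56% in controls and 64% to 68% with F-CaST. Standard errors of the T2 group difference:
- Scenario A: completers 0.65, likelihood-based model 0.51. Variance ratio (0.65/0.51)^2 = 1.62.
- Scenario B (stronger dependence): completers 0.65, likelihood-based model 0.56. Variance ratio (0.65/0.56)^2 = 1.35.

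The completers-only variance is about 35% to 60% larger.

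**4. Bias on the contrast the plan tests.** The time-by-group interaction concerns change over time, so change from T1 is the relevant quantity.
- Same simulation, completers only: 1.85 to 1.94 points. Shortfall (2 - 1.85)/2 = 7.5% and (2 - 1.94)/2 = 3%.
- A separate simulation of the change contrast: 1.92 to 2.00 points, a shortfall of 4% to 0%.
- Raw T2 difference, for comparison: completers 1.68 to 1.82, likelihood-based model 1.98 to 2.00.

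**5. Dependence on the assumptions.** Large simulation with no true effect, total SD 1, correlation between visits 0.5, completers only, change from T1. Retention is given as F-CaST v control. The strength of the link between staying and the score was varied from 0.3 to 0.7.

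| Retention | Staying depends on observed T2 score: bias at T2 | Staying depends on the man's own T4 deviation: bias at T4 |
|---|---|---|
| 60% v 60% | about 0 | about 0 |
| 70% v 50% | -0.04 to -0.10 SD | -0.07 to -0.15 SD |
| 80% v 40% | -0.09 to -0.21 SD | -0.13 to -0.31 SD |

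In the middle column the bias at T3 and T4 was about 0. At an assumed SD of 1.8, the 70% v 50% row is 0.04 x 1.8 = 0.07 to 0.10 x 1.8 = 0.18 points at T2, and 0.07 x 1.8 = 0.13 to 0.15 x 1.8 = 0.27 points at T4. The middle column is dropout at random, which a likelihood-based model handles. The last column is dropout not at random, which a mixed model alone does not cure.

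**The case against.** The strongest reply is that the article names a model and never says that only completers will be analysed. The same ANOVA can be run on imputed data, and missing-data rules usually sit in a full protocol or SAP, neither of which is shown. It is fair that the article does not declare a completers-only analysis. The point stands because it concerns the method that is stated: used as written, the ANOVA needs complete sets of scores.

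Second, losing completers was budgeted. That also stands: about 14 per arm is what the sample size allowed for, so there is no shortfall in power against the plan. The loss is relative to a better use of the same data.

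Third, no section says that men who leave the TC go unassessed at T2 to T4. The link from leaving to missing data is an inference. It is a reasonable one, since everyday performance is framed as performance within the TC and behaviour data come from TC counselors, but it must be labelled as such.

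Fourth, the simulated bias rests on assumed inputs, and dropout that depends on observed scores favours the likelihood-based model by construction. This too stands.

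A reader might also apply the Background statement that "the estimated therapeutic community (TC) dropout rates stands up to 71" per cent and conclude that only 48 x 0.29 = 13.9, about 14 men, would be analysed. The documents do not support that. The figure carries no time window, the Setting section says that TC treatment usually lasts 1 to 1.5 years, and the last assessment here is the 3-month follow-up. The trial's own planning figure is 40%.

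**Conclusion.** The concern holds in a limited form. The stated ANOVA would use about 29 of 48 men at the planned dropout and discard scores already collected from about 19. This follows from the method and the 40% figure, given that the 40% are men with at least one missed assessment. Lost precision is the surer cost, about 35% to 60% in variance under the assumptions shown.

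Selection bias is a risk, not a demonstrated error. It needs visits to be missed mainly through leaving the TC, and retention or its mechanism to differ between arms; with both equal it is about zero. On change from T1 it was about 0% to 8% of a 2-point effect in the illustrative scenarios, and larger where the retention gap was wide or dropout was not at random. A reader might infer that the COPM result will be seriously biased, or biased in a known direction. The documents give no SD, visit correlation, retention by arm or dropout mechanism, so neither can be claimed. This is a cheap improvement that should be made, not a critical fault.

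**What to change.** For COPM and the other repeated continuous scores, replace the ANOVA with a likelihood-based linear mixed model: SPSS MIXED, REML, unstructured covariance across visits, Satterthwaite degrees of freedom. Enter T1 to T4 all as outcomes, with visit effects, a common T1 mean for both arms, and group-by-visit effects at T2, T3 and T4. State the group contrast at each post-baseline visit.

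Keep T1 as an outcome rather than a covariate, and do not restrict the model to men with a post-baseline score. Either choice would exclude men who leave before T2, which is again selection after randomisation. Because T1 precedes allocation, all 48 randomised men can then contribute.

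Add one sensitivity analysis for dropout not at random, for example assigning no gain from T1 to men who left the TC. Say also that, for men who have left, the main model describes performance as if they had continued like comparable men who were observed.

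The cost is a change of wording and a little more analysis work, with the same data and software. The main model rests on a missing-at-random assumption, which the sensitivity analysis examines. The change is best made before outcome data are seen by group.

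### Partial eta squared is defined as if it were ordinary eta squared and named as the measure of clinical meaningfulness, while the COPM difference that sized the trial is not carried into the stated analysis

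*Protocol article*

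**What the plan says.** The Data analysis section plans a repeated-measures ANOVA with two groups and four time points, testing group, time and their interaction. It then states: "To assess the clinical meaningfulness of the outcomes, the Partial Eta squared in ANOVA effect size will be calculated". The next sentence gives the definition: "Partial Eta squared is interpreted as the proportion of the total variability in the dependent variable" that is attributable to the independent variable. Values of 0.01, 0.06 and 0.14 are labelled small, medium and large. Significance is a separate criterion: "Statistical significance will be set at p < 0.05".

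The Sample size section uses a different yardstick. The trial is sized to "detect a minimally clinically important difference of the primary outcome measure of everyday (occupational) performance" (COPM) "with 80% power and a significance level of 0.05", and "to account for a 40% dropout", giving 24 men per arm. Neither the MCID value nor an SD is printed. The Data analysis section does not mention the MCID.

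**The concern.** There are two separate problems.

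1. **The definition is wrong for this design.** The share of total variability is SS_effect/SS_total. Partial eta squared divides by SS_effect + SS_error only. The two agree in a one-way ANOVA but not in a 2×4 mixed ANOVA. For the interaction, stable differences between men and the other effects leave the denominator. For the group effect, differences between men are the error term, so the gap is smaller. A reader who follows the stated interpretation will overstate how much variability the treatment explains.

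2. **A variance ratio does not measure clinical meaning.** It has no direction and no COPM units, and it moves with the correlation between visits. In samples this small, chance alone often lifts it past the lowest label. The design section calls a COPM difference clinically important, while the analysis section uses something else. The report could therefore describe an effect as large without saying how it compares with the difference the trial was built to detect.

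**Working it through.** **Inputs from the protocol article.** 24 per arm, 48 in total; 40% dropout; 80% power; alpha 0.05 (two-sided assumed); 2×4 repeated-measures ANOVA; cuts 0.01, 0.06 and 0.14.

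**Assumptions.** Complete-case analysis after the full dropout; equal correlation ρ between visits (0.5, range 0.3 to 0.7); unit SD at each visit; sphericity; for the non-null case, no change in controls and a constant effect at T2, T3 and T4.

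**The plan's own figure.** 24 × 0.6 = 14.4, so about 14 completers per arm (N = 28). In reverse, 14/0.6 = 23.3, rounded up to 24, so the dropout step is consistent. A two-sample t-test with 14 per arm has 80% power for a standardised difference of 1.10. Whether that equals the MCID cannot be checked without its value and an SD. I use 1.10 SD as the illustrative effect.

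**Partial against ordinary eta squared, large-sample values** (effect a = 1.10, ρ = 0.5, per observation):
- Interaction: a² × (0.75 × 0.25)/4 = 1.21 × 0.1875/4 = 0.0567. The time component has the same value.
- Group: (0.75a)²/4 = 0.825²/4 = 0.1702.
- Interaction error: (1 − ρ) × 3/4 = 0.375. Group error: ρ + (1 − ρ)/4 = 0.625.
- Total: 0.375 + 0.625 + 0.0567 + 0.0567 + 0.1702 = 1.284.
- Interaction: partial 0.0567/(0.0567 + 0.375) = 0.131; ordinary 0.0567/1.284 = 0.044.
- Group: partial 0.1702/(0.1702 + 0.625) = 0.214; ordinary 0.1702/1.284 = 0.133.

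Both statistics are biased upwards in small samples. Means over simulated trials with 14 per arm:

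| Effect (ρ = 0.5) | Partial | Ordinary | Ratio |
|---|---|---|---|
| Interaction | 0.17 | 0.06 | about 3 |
| Group | 0.24 | 0.15 | about 1.6 |

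**Direction.** The effect enters only as a². A 1.10-SD harm therefore gives the same interaction value as a 1.10-SD benefit, about 0.17.

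**Visit correlation.** With the same 1.10-SD effect, mean interaction partial eta squared is 0.13 at ρ = 0.3, 0.17 at 0.5 and 0.23 at 0.7. It crosses the 'large' cut of 0.14 although the men gain nothing more.

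**Labels when there is no effect.** Partial eta squared then follows Beta(df1/2, df2/2). Equivalently, P(value ≥ e) = P(F > [e/(1 − e)] × df2/df1). For e = 0.01 at N = 28, the F threshold is 0.0101 × 26 = 0.263 for both effects.

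| N | Effect (df) | P(≥ 0.01) | P(≥ 0.06) | Value at p = 0.05 |
|---|---|---|---|---|
| 28 | Group (1, 26) | 61% | 21% | 0.140 |
| 28 | Interaction (3, 78) | 85% | 18% | 0.095 |
| 48 | Group (1, 46) | 50% | 9% | 0.081 |
| 48 | Interaction (3, 138) | 71% | 4% | 0.055 |

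The null mean is 1/(N − 1): 1/27 = 0.037 or 1/47 = 0.021, already above the 'small' cut. At N = 28 a group effect that only just reaches significance sits practically on the 'large' cut, so the label adds little to the p-value. With a sphericity factor of 0.7 at N = 28, the interaction figures become 78% and 20%, which leaves the message unchanged.

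**The case against.** The strongest reply is that this is one badly worded sentence in a condensed article. The definition changes neither the computed statistic nor the ANOVA nor its p-values. The labels are conventional, no cut is declared to mark a clinically meaningful result, and an unseen SAP may well compare COPM scores with the MCID. Much of this stands, and it limits the point. Four stronger readings are tempting but not supported:

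- **That the MCID is never used.** It drives the sample size. What can be said is that the stated analysis does not take it up.
- **That noise will be declared meaningful, or that type I error rises.** The p < 0.05 criterion is separate and unaffected. Under the null, reaching 'medium' is a minority outcome: 18–21% with 28 men and 4–9% with 48.
- **That the report could not say whether the MCID is reached.** Descriptive statistics by group are planned for the primary outcomes, so the comparison would be possible. The article simply names another measure for the purpose.
- **That partial eta squared is several times too large throughout.** The roughly threefold gap belongs to the interaction. For the group effect it is about 1.6-fold.

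The reply does not remove the core. The article does more than leave the interpretation to another document. It states a definition that is wrong for its own design, and it assigns clinical meaning to a statistic that cannot carry it.

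**Conclusion.** The point holds in this limited form and should be corrected. The definitional error and the null probabilities do not depend on any assumed treatment effect. The null probabilities do depend on N (28 if the full 40% drop out and only complete cases are analysed, 48 if nobody does) and, for the interaction, on sphericity. The 0.17 against 0.06 and 0.24 against 0.15 are illustrations. They rest on 14 completers per arm, a 1.10-SD effect and a correlation of 0.5, none of which the article prints. The 0.06 and 0.15 are small-sample means; the large-sample shares are about 0.04 and 0.13. The consequence is misleading interpretation, not an invalid test.

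**What to change.** In the Data analysis section:

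1. Define partial eta squared as SS_effect/(SS_effect + SS_error), and drop the reference to total variability.
2. Keep it, if wanted, as a supplementary descriptive figure, and remove its role in judging clinical meaningfulness.
3. State that clinical meaningfulness will be judged by the between-group difference in COPM points with its 95% CI, read against the MCID used for the sample size, and print that MCID value.

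The article does not name a primary time point, so the authors must say at which visit or visits the difference is read. The proportion of men in each arm who improve by at least the MCID is an optional addition; with about 14 per arm it would be imprecise and would discard information. The cost is a few sentences and a small amount of extra analysis and reporting. No new data, visits or participants are needed.
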